#### 2.2.6 Data collection and analysis

The new tool and PG-SGA will be used to collect data to assess malnutrition in NPC patients. The external validation will be performed using the ROC curve, AUC value, and calibration plot. The ROC curve will be performed, and the AUC value will be calculated using MedCalc software. The calibration plot will be generated using the “rms” package of R software 4.2.1.

#### 2.2.7 Study procedure

At the Second Affiliated Hospital of Guangxi Medical University, 100 well-nourished and 100 malnourished NPC patients will be recruited, using PG-SGA as the standard for malnutrition assessment.The new tool will be utilized to assess the nutritional status of these 200 NPC patients.The assessment results obtained with the new tool will be analyzed against the PG-SGA to calculate AUC for evaluating NPC patients’ nutritional status. Additionally, ROC curves and calibration plots will be generated to visually demonstrate the accuracy and reliability of the new tool.

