#### 2.1.5 Sample size

The sample size calculation was based on previous research conducted by Riley et al. [21]. We included 15 predictor variables in the risk factor questionnaire. Based on the findings reported by Song et al. [22], a PG-SGA score of 2 or higher was utilized as a diagnostic criterion for malnutrition. The incidences of malnutrition and well-nourished in NPC patients were 0.599 and 0.401, respectively [22]. For logistic regression models with outcome proportions of 0.4, the corresponding max(R^2^_cs_) value is 0.74 [21]. For binary outcome, R^2^_cs_ = 0.5* max(R^2^_cs_) = 0.37. The sample size was calculated using the R language (version 4.2.1) with the pmsampsize package. The programming to calculate sample size was “(type = “b”, rsquared = 0.37, parameters = 15, prevalence = 0.401)”. After comparing the calculated sample sizes, the largest sample size was 370.

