#### 2.2.2 Study design

The study is designed as a prospective, cross-sectional diagnostic study.

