#### 2.2.5 Sample size

Currently, there are no generally accepted methods for calculating the sample size required for external validation of risk prediction models. However, prior investigations [23, 24] have put forth a recommendation that external validation studies should incorporate no fewer than 100 events and 100 nonevents to ensure accurate and precise estimates of performance measures. Thus, to comply with this recommendation, at least 100 well-nourished NPC patients and 100 malnourished NPC patients will be recruited to validate the new tool in Phase II.

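### The fixed 100:100 outcome quota in Phase II conflicts with the stated minimum and the cross-sectional design, and shifts the intercept of the external calibration plot unless prevalence is near 50%

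*Protocol article*

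**What the plan says.** Three Phase II sections describe the sample differently.

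- Section 2.2.2: "The study is designed as a prospective, cross-sectional diagnostic study".
- Section 2.2.5 cites a recommendation that "external validation studies should incorporate no fewer than 100 events and 100 nonevents" and concludes that "at least 100 well-nourished NPC patients and 100 malnourished NPC patients will be recruited to validate the new tool in Phase II". This is a minimum for each outcome group.
- Section 2.2.7: "100 well-nourished and 100 malnourished NPC patients will be recruited, using PG-SGA as the standard for malnutrition assessment". It continues: "The new tool will be utilized to assess the nutritional status of these 200 NPC patients". Here the minimum has become an exact count for each outcome group and an exact total.

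On analysis, section 2.2.6 states: "The external validation will be performed using the ROC curve, AUC value, and calibration plot". Section 2.2.7 again names AUC, ROC curves and calibration plots.

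Phase I works the other way round. Section 2.1.8 recruits 370 patients and then divides them by PG-SGA, so the tool is fitted at whatever prevalence occurs. For planning, section 2.1.5 states that "a PG-SGA score of 2 or higher was utilized as a diagnostic criterion for malnutrition", and gives the expected split: "The incidences of malnutrition and well-nourished in NPC patients were 0.599 and 0.401, respectively".

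**The concern.** A tool that outputs an individual's risk carries an intercept, and the intercept reflects the prevalence at which the tool was fitted. If the validation sample is filled by outcome group to 50:50, its observed proportion is set by the recruiter and not by the second hospital's patients. Predicted and observed risks then differ by a constant on the logit scale, however good the tool is.

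Calibration is one of the two kinds of performance that the protocol assesses (with discrimination), and the nomogram is meant to let staff read off an individual's risk. A distorted intercept can make a sound tool look wrong. It can also hide a real error of opposite sign, because the plot shows the sum of the true intercept error and the shift caused by the quota.

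**Working it through.** **Inputs.** Prevalence of malnutrition 0.599, with 0.401 well-nourished (2.1.5). Other PG-SGA prevalences in the Discussion: 37.4% (score of 4 or more) and 53.1%. Phase II sample: 100 + 100 (2.2.7). Planned R²cs 0.37 with 15 parameters (2.1.5).

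**The plan's own figure.** The three Phase I criteria for a binary outcome are:

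- Shrinkage 0.9: 15 / [(0.9 − 1) × ln(1 − 0.37/0.9)] gives 284.
- Optimism 0.05, with S = 0.37/(0.37 + 0.05 × 0.74) = 0.909: 15 / [(S − 1) × ln(1 − 0.37/S)] gives 316.
- Outcome proportion within ±0.05: (1.96/0.05)² × 0.401 × 0.599 = 369.1, rounded up to 370.

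The maximum is 370, as stated. The inputs are therefore read correctly, and Phase I is planned at natural prevalence.

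**Shift caused by the quota.** With equal numbers sampled from each class and source prevalence π, the observed logit in the sample equals the true logit plus ln[(1 − π)/π].

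| Source prevalence | Shift (logits) | Predicted 20 / 40 / 60 / 80% appears as |
|---|---|---|
| 59.9% | ln(0.401/0.599) = −0.401 | 14.3 / 30.9 / 50.1 / 72.8% |
| 53.1% | ln(0.469/0.531) = −0.124 | 18.1 / 37.1 / 57.0 / 77.9% |
| 50% | 0 | 20 / 40 / 60 / 80% |
| 37.4% | ln(0.626/0.374) = +0.515 | 29.5 / 52.7 / 71.5 / 87.0% |

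For example, at 59.9% a predicted 60% has odds 1.5. Multiplied by 0.669 this gives 1.004, or 50.1%.

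**How often a perfect tool would be flagged.** A perfectly calibrated model with a normally distributed linear predictor was simulated, and 100:100 samples were drawn from it. Calibration-in-the-large was tested at 5% with the linear predictor as offset.

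- At 59.9%, the mean estimate was about −0.40. The tool was falsely flagged in 93%, 78% and 58% of validations for linear-predictor SD 1.0, 1.5 and 2.5 (AUC 0.74, 0.81, 0.90). At SD 2.0, which corresponds to R²cs of about 0.37, the rate was about 66%.
- At 37.4%, the rates were 82% to nearly 100%.
- At 53.1%, they were 0.2% to 3%.
- With 200 consecutive patients at 59.9%, the mean estimate was about 0 and 4% to 6% were flagged.

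**What the quota leaves alone.** The shift is a constant, so the logit slope is unchanged. The simulated AUC at 59.9% was 0.740 / 0.815 / 0.896 under the quota, against 0.740 / 0.813 / 0.897 in the population.

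**Does the total of 200 fit a minimum rule?** Reaching 100 well-nourished patients consecutively takes 100/0.401 = 249 patients on average, of whom 249 × 0.599 ≈ 149 are malnourished. For a 95% chance of at least 100 well-nourished patients, the binomial tail requires 282. A total of exactly 200 does not match that rule at the planning prevalence.

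**The case against.** The strongest defence is that 2.2.5 is the governing sample-size section and sets a floor, so 2.2.7 may only restate the target in short form. Enrolling until both floors are met would avoid the problem. That reading is possible, but 2.2.5 does not mention consecutive enrolment, and the exact total in 2.2.7 does not fit it at 59.9%. The conflict needs resolving in the text.

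A second defence is that a prevalence correction belongs in an analysis plan. This is fair as to the method, and its absence here is not the point. The recruitment rule, however, is fixed in this document, and sampling fractions that are never logged cannot be recovered later.

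Third, the protocol plans a plot and gives no calibration test or pass rule. That stands: the 66% shows how visible the shift would be, and is not the error rate of a planned test.

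A reader might infer more than the text supports:

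- *That the plot must mislead at any prevalence.* It does not. The shift is zero at 50%, and at 53.1% it would rarely be noticed with 200 patients.
- *That the shift could be much larger, using the 16.8% malnourished before radiotherapy in the Discussion.* That figure is by GLIM criteria, whereas Phase II classifies by PG-SGA, so it cannot serve as the source prevalence here.
- *That clear-cut cases will be picked and the AUC inflated.* Nothing in the protocol describes this. Section 2.2.3 applies predefined criteria, and the quota alone leaves the AUC unchanged.
- *That this is two-gate sampling.* Both groups enter under one set of criteria at one hospital. It is an outcome quota within a single source.

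**Conclusion.** The concern holds, conditional on prevalence. As written, 2.2.7 contradicts 2.2.5 and 2.2.2 and forces 50% malnourished on the validation of a tool developed at natural prevalence. On the protocol's own planning figure, the calibration intercept of a perfect tool is displaced by −0.40 logits, about 10 percentage points at a predicted 60%. The displacement would be positive (+0.52) if malnutrition meant a PG-SGA of 4 or more, and minor (−0.12) at 53.1%.

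This assumes that the second hospital's source prevalence equals the figure used, that patients within each class are representative, and that no correction is applied. The 66% further assumes a normally distributed linear predictor at the planned R²cs. Discrimination and the logit slope are not compromised by the quota; only calibration-in-the-large is. The matter should be settled before Phase II recruitment, because the information needed to repair it is lost if it is not recorded during screening.

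**What to change.** Reconcile 2.2.7 with 2.2.5. Preferred text for 2.2.7: consecutive eligible patients will be enrolled until at least 100 well-nourished and at least 100 malnourished patients, classified by PG-SGA, have been reached; all enrolled patients will be analysed.

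*Cost.* At 59.9%, about 250 patients are expected rather than 200, and about 282 should be allowed for a 95% chance of 100 well-nourished. Surplus patients need PG-SGA in any case to be classified, but would also need the tool's predictors, which may include blood indices. Recruitment would take longer, and 2.2.3 currently places it in January 2024.

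*Alternative, if 100:100 is kept.* Fill each class consecutively. Log the PG-SGA class of every eligible patient screened, including those met after a class is full. Then correct the calibration analysis in one of two ways:

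- weight each patient by the inverse of the class sampling fraction; or
- add ln(sampling fraction of malnourished / sampling fraction of well-nourished) to the tool's intercept before plotting. With about 149 malnourished and 100 well-nourished screened, this is ln[(100/149.4)/(100/100)] = −0.40.

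This needs no extra patients in the analysis, only a screening log and one added analysis step. Section 2.2.2 should then say that patients were sampled by outcome class.

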### 2.3 Study flow chart

2.3.1 The flow chart of Phase I is shown in Fig 1.

**Fig 1 pone.0300067.g001:**
[figure not shown]
The flow chart of Phase I.

2.3.2 The flow chart of Phases II is shown in Fig 2.

**Fig 2 pone.0300067.g002:**
[figure not shown]
The flow chart of Phases II.

### 2.4 Ethics and dissemination

The proposed study will conform to the international guidelines of Good Epidemiology Practice and the Declaration of Helsinki. Ethical approval was obtained from the Ethical Committee of the First Affiliated Hospital of Guangxi Medical University (NO. 2022-KT-GUIWEI-005) and the Second Affiliated Hospital of Guangxi Medical University (NO. 2022-KY-0752). Furthermore, prior to data collection, written consent will be obtained from all NPC patients.

### 2.5 Quality control

To ensure the rigor of the study, several methods and strategies have been implemented. Firstly, a rigorous design process was followed for the risk factor questionnaire, which involved extensive solicitation of expert opinions and suggestions as well as a thorough literature search. The initial questionnaire was reviewed and revised by experts, and pre-testing was conducted on 10% of the sample size among NPC patients. The feedback collected was used to revise the questionnaire.

Furthermore, two investigators will undergo unified training, and they will be responsible for collecting and managing the data from NPC patients. To prevent the occurrence of duplicate records, the data was matched independently with the unique ID numbers of participants.

After each patient completes the questionnaire, the interviewer will check on-site, and the participant will be asked again to complete the questionnaire if there are any omissions. All data entry will be double-checked and double-entered.

### 2.6 Patient and public involvement statement

We involved NPC patients in the development of the risk factor questionnaire. We sought feedback from patients on the questionnaire’s clarity, ease of understanding, and acceptability. During the study’s implementation phase, we will work closely with NPC patients to ensure that they understand the study’s purpose and procedures. Finally, we will seek patients’ feedback on the new nutritional assessment tool’s usefulness and ease of use.

### 2.7 Preregistration

The study was pre-registered in the Chinese Clinical Trial Registry (Registration No.: ChiCTR2300071550)

## 3 Discussion

Malnutrition is very common among NPC patients, and it can lead to adverse outcomes [25–27]. Pan’s survey of 102 NPC patients found that 5.3% (5/95), 19.6% (18/92), and 94.8% (36/38) of patients had NRS2002 scores <3 and PG-SGA scores ≥4 before induction chemotherapy, before radiotherapy, and at the end of radiotherapy, respectively [7]. Similarly, Wan surveyed 113 NPC patients and found that 16.8% of patients were malnourished before radiotherapy, while 91.2% of patients were malnourished at the end of radiotherapy according to the GLIM criteria [9]. Additionally, a survey conducted in Kenya discovered that 35% of NPC patients experienced significant weight loss [28]. Furthermore, another research group has found that 53.1% of the NPC patients were malnourished according to PG-SGA [8]. Song surveyed 2819 NPC patients from multiple cities in China and found that patients with PG-SGA score ≥2 and PG-SGA score ≥4 accounted for 59.9% and 37.4%, respectively [22]. Malnutrition could weaken the immune system, prolong hospital stays, and affect treatment efficacy [10–12]. Moreover, several studies have shown that malnutrition is linked to poorer survival outcomes in NPC patients [13, 29].

There are different studies using different malnutrition assessment tools to identify risk factors for malnutrition in NPC patients. Jin conducted a retrospective study on 117 patients with stage III-IVa NPC and found that those who experienced grade ≥ 3 radiation-induced oral mucositis during radiotherapy had worsened malnutrition, and pre-albumin level was identified as a predictive marker for weight loss in this patient population [30]. In another study, Hong found that moderate nutritional status before radiotherapy, high side effect score, depression, the late stage of the disease, female gender, and old age were the risk factors for poor nutritional status in NPC patients [31]. Similarly, Irungu discovered that stage IV NPC was a predictive marker for weight loss and low serum albumin levels [28]. Chen’s research revealed that NPC patients with higher symptom severity, more severe trismus, higher levels of depression, completion of treatments within 1 year, advanced stage, and female gender were more likely to be at risk of malnutrition or have malnutrition [32]. Qiu discovered that concurrent chemotherapy, Karnofsky performance status, radiation techniques, insomnia, N stage, body mass index, and global quality of life were independent prognostic factors for significant weight loss in NPC patients [33]. Finally, Xueyan utilized PG-SGA to assess malnutrition and identified economic status, overall quality of life, oral mucositis, anemia, prealbumin, weight loss during chemoradiotherapy, and clinical stages as factors for malnutrition in NPC patients [34].

Compared to previous studies, PG-SGA will be used to identify the risk factors for nutritional risk in NPC patients. The PG-SGA has been recommended by the Oncology Nutrition Dietetic Practice Group of the Academy of Nutrition and Dietetics as a comprehensive nutrition assessment tool for cancer patients [35]. Moreover, this study will comprehensively analyze the demographic data, disease status, physical examination, and blood sampling. Finally, our study had a large sample size. The identification of risk factors will provide a theoretical basis for nutritional screening, malnutrition prevention, assessment, and nutritional support in NPC patients. Identifying these risk factors would be beneficial for clinicians and healthcare practitioners in the management of NPC patients.

While malnutrition is a common problem, there is no universally accepted gold standard for the assessment of malnutrition [36]. Interobserver variability, difficulty in reproducibility, technician experience, time-consuming nature of some tools, expense of others, lack of validation for some tools, etc. may be the main reasons for the lack of a gold standard for malnutrition assessment. Additionally, the heterogeneity of the population being assessed as well as the setting in which malnutrition is assessed can also affect the definition of a gold standard.

The PG-SGA, Minimal Nutrition Assessment (MNA), and Global Leadership Initiative on Malnutrition (GLIM) are commonly used nutritional assessment tools. However, commonly used malnutrition assessment tools have many shortcomings. PG-SGA is generally considered the gold standard for assessing malnutrition in cancer patients, but it is complex and time-consuming, and its results also depend on the experience of the observer [37]. Although GLIM has unified the diagnostic criteria for malnutrition to a certain extent, it remains an expert consensus, and its clinical effect still needs to be verified [38]. The applicability of MNA to Asians may be limited due to the absence of race-specific metrics, and the definition of BMI in MNA may need to be adapted to account for racial differences [19].

This study will develop the first malnutrition assessment tool for NPC patients based on risk factors for malnutrition. This new tool will be proven to be an effective tool and useful for clinical applications, which will help to unify the standard of malnutrition assessment for NPC patients, assess malnutrition early, give nutritional treatment and support in time, improve work efficiency, and reduce adverse outcomes caused by malnutrition.

## 4 Limitation of study

Compared to other malignancies, NPC is a rare neoplasm exhibiting marked ethnic predisposition and regional variations, with a high incidence in densely populated regions of South China and Southeast Asia. The potential limitations of this investigation include a restricted geographical range and a limited sample size, as the study will be conducted solely in China. Subsequent studies should extend beyond China, ensuring the validation of the study’s findings. Furthermore, the exclusive use of an Asian population in this study limits the generalizability of our results to other ethnicities.

This study only comprehensively analyzes objective factors such as socio-demographic data, lifestyle habits, treatments, disease state, anthropometry, and blood indices, but does not analyze subjective indicators such as psychology.

## 5 Conclusions

This study will help to clarify the risk factors for malnutrition in NPC patients, provide specific nutritional assessment tools for NPC patients, improve the work efficiency of hospital staff, and help medical staff to assess malnutrition earlier and faster and provide timely nutritional support and treatment to reduce the incidence of malnutrition in NPC patients.
